### Statistical analysis

All continuous outcomes will be analyzed as a change from baseline with linear mixed models (LMM). These have the advantage of using all available data of each subject and they also offer the opportunity to choose an appropriate covariance structure reflecting the potential dependence due to repeated measurements (43). Adjustment for baseline measure will be chosen as this increases statistical power and accounts for regression to the mean (44). Missing values will be substituted using multiple imputations (with 50 imputations per missing value) to estimate missing scores by evaluating the relationships between observed and missing scores as well as baseline scores. For dichotomous outcomes, we will calculate logistic regression analyses that are adjusted for baseline values and time-to-event analyses (Kaplan–Meier survival analyses and Cox proportional hazards regression).

#### Primary analysis

The primary analysis for all the outcomes will be an LMM analysis on the intention-to-treat sample (ITT analysis), which includes all randomized participants. These analyses will include a random intercept for the participant and adjustment for baseline measure. The following will be entered as a fixed effect: time, study group, diagnosis of BPD, and the time X group interaction. A covariance structure will be chosen based on Akaike's Information Criterion (AIC) from a fixed set of candidate structures, namely a first order autoregressive (AR1), diagonal or scaled identity structure or heterogeneous versions thereof. The study hypothesis will be tested on the main effect for group. The “time x group” interaction will be reported to establish whether the between-group effect changes over the 1 year assessment period.

#### Sensitivity analysis

We will conduct sensitivity analyses to determine the robustness of our results for the main outcome (BPDSI). In an *adjusted analysis*, we will correct for the following baseline variables: age, sex as well as baseline severity and diagnosis of BPD. In a *per-protocol analysis*, we will include participants randomized to the intervention group only if they have used the intervention for at least 3 h and compare these to all participants in the CAU group.

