### Interventions

All participants are permitted to use any form of treatment, including psychotropic medication and psychotherapy. Following a pragmatic design approach, CAU is not influenced by the investigators (28). Participants in the control condition receive only CAU. In addition, they receive information regarding freely available self-help material on the internet, and they are offered access to the internet intervention after the last follow-up assessment.

Participants in the intervention group receive access to the unguided self-management intervention *priovi* in addition to CAU. They will be informed that priovi does not replace their ongoing psychotherapy but is merely an addition to it. The priovi intervention was developed and is owned by GAIA group, Hamburg, Germany. It is based on the principles of Schema Therapy. In Schema Therapy, problematic BPD behaviors and symptoms are connected with so-called schema modes, i.e., emotional states related to dysfunctional schemas such as mistrust/abuse or abandonment. Examples of typical schema modes in BPD patients include the *angry/impulsive child* mode (related to anger outbursts and impulsive behaviors) and the *detached protector* mode (related to problematic emotion-avoidance strategies such as dissociation). In Schema Therapy patients learn to identify their schema modes and to understand the biographical background of these modes. Further along, the treatment goals in Schema Therapy are also related to these modes and include helping the angry child mode find adequate ways to deal with anger or reassuring the detached protector mode so that patients can reduce their emotional avoidance and learn healthier strategies to deal with emotions and relationships.

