Priovi is comprised of eight modules that are organized in simulated dialogues and can be accessed over a period of 1 year. These modules are divided in a psychoeducation phase (BPD symptoms, human needs, childhood abuse, and modes) and an intervention and exercise phase (these are tailored to the modes of the user and include cognitive techniques, imagery exercises, and affirmative audios). Each session is tailored to the current mood state of the user and thus addresses the frequent mood shifts associated with BPD. It is recommended to use the intervention twice a week for half an hour. Participants using the intervention on this regular basis can complete the full content in about 6 months, but it is recommended to use the intervention for the full year to continue with the exercises. A full description of the intervention can be found elsewhere (13).

The intervention will be unguided but participants who have not logged onto the intervention until the fifth day will receive a reminder that will once again explain the login procedure. Also, the intervention will send automated messages that are designed to motivate the user to engage with the intervention and the content covered in the intervention on a regular basis. Participants will also be able to contact a hotline to receive technical support. The hotline will refer to the treating psychiatrist / psychotherapist for management of acute crises.

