### Sample size

The sample size calculation is based on the expected difference between the intervention and the control group in the severity of BPD (measured with the BPDSI) at the 12 months assessment. Based on an estimated effect size of Cohen's *d* = 0.40, a power of 0.80 and an alpha level of 0.05, 100 participants are required in each condition resulting in a target sample size of *N* = 200. The effect size estimate was based on a recent meta-analysis (6), where the between-group effect for add-on designs (in which both groups received CAU and one group received an additional BPD therapy) was *g* = 0.40.

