### Randomization

Participants are randomized equally (1:1) into two groups (intervention or control). Randomization is stratified by the presence of a diagnosis of BPD (probable vs. definite diagnosis of BPD). Block randomization with variable block sizes is used. The allocation schedule was created by an independent investigator with a computerized random number generator; the other investigators are blind to this schedule. The allocation sequence is concealed from participants and all trial staff. Only the unblinded trial staff is informed about the randomization outcome. The unblinded trial staff will not be included in data collection or evaluation and is instructed not to inform the raters about the randomization outcomes. Additionally, all participants are informed three times (at the end of the first interview, via the mail invitation for the second interview and at the beginning of the second interview) not to disclose their group assignment to their interviewer and to reserve questions about the usage of the intervention program exclusively for priovi support or the study team.

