#### Subgroup analyses

We will also perform subgroup analyses to establish whether certain subgroup variables moderate the effect of the intervention on the main outcome (BPDSI). The hypothesis of difference in treatment effects will be tested using the “group X subgroup variable” interaction. In one subgroup analysis, we will test the influence of a diagnosis of BPD (as assessed during the SCID screening interview). In another subgroup analysis, we will test the influence of concomitant psychotherapy (as self-reported by the participants).

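### The per-protocol comparison drops low users from the intervention arm only, so it is a non-randomised contrast and cannot show that the ITT result is robust

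*Protocol article*

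**What the plan says.** The Primary analysis section uses the "intention-to-treat sample (ITT analysis), which includes all randomized participants". The Sensitivity analysis section then sets out two checks of how robust the BPDSI result is. One is a covariate-adjusted model. The other is a per-protocol analysis that admits intervention participants "only if they have used the intervention for at least 3 h and compare these to all participants in the CAU group". No adjustment for what drives use is named for this second check; the age and sex adjustment belongs to the first.

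The Interventions section gives the context for 3 h: "It is recommended to use the intervention twice a week for half an hour". At that pace the content takes about 6 months. The same section says of control participants that "they are offered access to the internet intervention after the last follow-up assessment".

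On a related matter, the Subgroup analyses section ties the BPD-diagnosis subgroup to the screening interview. For the second subgroup it says only that "we will test the influence of concomitant psychotherapy (as self-reported by the participants").

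**The concern.** Randomisation makes the arms comparable as randomised. The 3 h rule removes one kind of participant from the intervention arm, and that person's counterpart in CAU cannot be identified and stays in. If use is related to prognosis, the remaining users differ from the CAU arm before any treatment effect is counted. The contrast then mixes effect with selection, and agreement or disagreement with ITT says little about robustness.

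The Exploratory analyses section itself expects adherence and outcome to be linked, citing a depression intervention. That makes a non-zero correlation plausible, but it does not separate selection from a real dose effect.

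What is at stake is interpretation. The Discussion concedes that the sample may prove too small and that ITT may miss significance. That is when a more favourable per-protocol estimate would be most tempting to read as support.

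**Working it through.** **Step 1: the plan's own figure.** The Sample size section states "a power of 0.80 and an alpha level of 0.05, 100 participants are required in each condition"; its effect size is d = 0.40 and its total is 200. Allocation is 1:1 (Randomization section). By the normal approximation, two-sided, n per arm = 2(1.960 + 0.842)²/0.40² = 98.1, rounded up to 99. The t-test solution is 99.08, so 100 per arm, with power 0.804. The stated figure reproduces and is not in dispute.

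**Step 2: model for the per-protocol contrast under zero effect.** All 100 CAU participants are kept. A share q of the 100 intervention participants is kept because a latent normal use variable exceeds its cut-off c, where c is the (1 − q) normal quantile. That variable correlates r, in the favourable direction, with the baseline-adjusted outcome (SD 1). Complete data and a single comparison of means stand in for the mixed model. Both q and r are assumptions, as the article gives neither.

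- λ = φ(c)/q
- Spurious difference b = rλ
- Variance among the users kept: v = 1 − r²λ(λ − c)
- SE = √(v/(100q) + 1/100)
- Two-sided rejection = Φ(b/SE − 1.96) + Φ(−b/SE − 1.96)

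**Step 3: one case in full.** Take q = 0.6 and r = 0.2. Then c = −0.253, φ(c) = 0.386 and λ = 0.644, so b = 0.129. Next, v = 1 − 0.04 × 0.644 × 0.897 = 0.977 and SE = √(0.977/60 + 0.01) = 0.162. Rejection is 12.5%, of which 12.2% favours the intervention (nominal 2.5% on that side).

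**Step 4: the range.** Spurious difference in SD, with two-sided rejection (nominal 5%):

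| Share reaching 3 h | r = 0.1 | r = 0.2 | r = 0.3 |
|---|---|---|---|
| 0.9 | 0.019; 5.2% | 0.039; 5.8% | 0.058; 6.9% |
| 0.8 | 0.035; 5.6% | 0.070; 7.6% | 0.105; 10.9% |
| 0.7 | 0.050; 6.2% | 0.099; 9.8% | 0.149; 16.3% |
| 0.6 | 0.064; 6.8% | 0.129; 12.5% | 0.193; 22.5% |
| 0.5 | 0.080; 7.5% | 0.160; 15.3% | 0.239; 29.1% |

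The largest value is 0.239/0.40 = 60% of the planned effect. A negative r gives the same sizes with the opposite sign.

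**Step 5: the threshold.** 2 × 0.5 h × 26 weeks = 26 h, and 3/26 = 11.5%. At the recommended pace of 1 h a week, 3 h is reached in three weeks.

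**Step 6: the psychotherapy subgroup.** Suppose use were measured after randomisation, the intervention moved uptake from 50% to 31% or 69%, and the correlation between the tendency to use psychotherapy and the outcome were 0.2 (all assumed). A simulation with no treatment effect then gives within-subgroup differences of 0.068 and 0.059 SD at 31%, and −0.059 and −0.071 SD at 69%. The two subgroups move together, so the interaction shifts by only about 0.01 SD. With no change in uptake the differences are essentially zero.

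**The case against.** The case on the other side has weight. The analysis is labelled a sensitivity analysis, sits behind ITT on all randomised participants, and carries no decision rule. A 3 h threshold is low, so it may exclude few people; if 90% reach it, the distortion is only 0.02 to 0.06 SD. The share and the correlation are not in the article, and baseline adjustment, if carried over, leaves only the residual correlation. All of this limits the size of the problem. It does not restore randomisation, and because size and direction are unknown the comparison cannot serve as a check of robustness. Nor is the comparison left open for a fuller document to settle: the article fixes both the filter and the comparator.

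A reader might go further in four ways that the article does not support:

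- *The trial's conclusion or type I error is compromised.* It is not; the hypothesis is tested on the ITT sample.
- *The comparison must flatter the intervention.* The article does not show that users have the better prognosis, and if sicker patients use the programme more the bias runs the other way.
- *The 3 h rule contradicts a required amount of use.* Use is only recommended, so this is a question of naming.
- *The psychotherapy subgroup is defined after randomisation.* The text is silent on timing. A baseline reading is open, and a condensed article may leave that detail, and a row in Table 1, to the analysis plan. The planned test is the interaction, which barely moves. The Discussion also reports that in an earlier, larger depression trial concomitant therapy did not differ between groups over 1 year.

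**Conclusion.** The point holds for the per-protocol analysis. As written, it is a non-randomised contrast selected on behaviour after randomisation, and it should not be offered as evidence that the ITT result is robust. Under zero true effect, the illustrated distortion runs from negligible (0.02 SD, 5.2% rejection) to substantial (0.24 SD, 29.1%). These figures rest on the assumed shares and correlations, complete data and a normal selection model. They show what could happen and do not predict what will. Since only a secondary conclusion is at stake, this should be changed but does not threaten the trial.

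The psychotherapy subgroup is a minor ambiguity: it may condition on use after randomisation, but nothing in the article says that it will.

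**What to change.** Replace the per-protocol comparison with a complier-average causal effect (CACE), or make that the main adherence analysis. Randomisation is the instrument and baseline covariates are included. In its simplest form the estimate is the ITT difference divided by the proportion of the intervention arm who comply. Noncompliance is one-sided by design, because CAU participants get access only after the last follow-up.

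Define compliance as any use, where it is plausible that assignment has no effect on non-compliers, and report the 3 h cut as a second threshold. At 3 h that assumption is doubtful: some benefit below the cut would be credited to compliers and inflate their estimate. If the 3 h versus all-CAU comparison is kept, label it non-randomised, supportive and minimal use, and do not cite it for robustness.

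For the psychotherapy subgroup, state that the T0 report defines it.

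The cost is a few lines of analysis plan and one extra model. The drawbacks should be stated: the exclusion restriction has to be assumed, and the interval is wider. With 60% compliance (assumed), an ITT difference of 0.40 becomes 0.40/0.6 = 0.67, and the interval widens by about the same factor. The test therefore largely repeats the ITT test. The CACE estimates the effect in users and is not independent confirmation of the primary result.

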#### Subgroup analyses

We will also perform subgroup analyses to establish whether certain subgroup variables moderate the effect of the intervention on the main outcome (BPDSI). The hypothesis of difference in treatment effects will be tested using the “group X subgroup variable” interaction. In one subgroup analysis, we will test the influence of a diagnosis of BPD (as assessed during the SCID screening interview). In another subgroup analysis, we will test the influence of concomitant psychotherapy (as self-reported by the participants).

#### Exploratory analyses

Further exploratory analyses will be conducted. One exploratory analysis will examine predictors and moderators of serious adverse events. Another analysis will deal with the adherence-outcome association as adherence has been shown to improve outcome in a self-management intervention for depression (45).

### Data management

The steering committee will perform internal audits to ascertain that this protocol is adhered to, all trial staff has the required qualifications and that the data quality is adequate (e.g., range checks for data values). During these audits, frequencies of serious adverse events will be compared between groups. The trial will be terminated prematurely if serious adverse events occur significantly more frequently in the intervention group. No independent Data Monitoring Committee has been established however and no interim analyses for the main outcome or other outcomes other than safety will be conducted.

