## Abstract

**Introduction:** Borderline Personality Disorder (BPD) is a prevalent condition that is often under-treated. This is partly because very few psychotherapists offer treatment for this disabling disorder. Internet-based self-management interventions could contribute to reducing the treatment gap but—mainly due to safety concerns—these have never been tested for BPD in controlled trials.

**Methods:** Patients with BPD will be recruited primarily via the internet and randomized to two groups: care as usual (CAU) alone) or the self-management intervention *priovi*® in addition to CAU. At the end of the diagnostic interview, all participants will discuss an emergency plan. The main outcome measure is the clinician-rated symptom severity using the BPD Severity Index (BPDSI). Secondary outcome measures include a range of self-reported scales, an SCID-diagnosis of BPD and several safety parameters including serious adverse events (e.g., a life-threatening event, hospitalization or suicide attempt).

**Discussion:** This trial will evaluate the effectiveness of the self-management intervention, *priovi*, in reducing symptoms of BPD. It will also assess the safety of its use in this target population. If successful, this intervention would be the first comprehensive internet intervention for the treatment of BPD and complement the wide range of internet interventions effective in treating other mental disorders, particularly depression and anxiety disorders.

**Trial Registration:** NCT03418142 (clinicaltrials.gov) on January 23rd 2018.

**Trial status:** recruiting, currently *N* = 108 (July 2018).

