## Introduction

Borderline Personality Disorder (BPD) is a common mental disorder characterized by a pervasive pattern of instability in interpersonal relationships, self-image and affect as well as marked display of impulsivity (1). The prevalence of BPD is about 2% with higher prevalence rates in women than in men (2, 3). In Germany, the annual treatment costs for BPD amount to about 15% of the total costs incurred for mental disorders (4). About 75% of these costs are due to inpatient treatment, which can be substantially reduced by effective treatment (5). Although a number of effective psychological treatments exist for BPD (6), only about one-in-four patients receive psychotherapy even in relatively well-developed health care systems (7). Reasons for this treatment gap include unavailability of trained psychotherapists. In one study involving over 150 psychotherapists, about one-in-five outrightly refused to treat patients with BPD “out of principle” (8).

Internet interventions are considered a viable option to help reduce the treatment gap in mental health (9). Broadly, these interventions can be divided into teletherapy interventions and self-management interventions (10). In *teletherapy interventions*, therapists communicate with their patients via the internet (e.g., e-mail or video chat). In *self-management interventions*, knowledge and techniques based on evidence-based psychotherapeutic methods are taught by an internet-based computer program instead of a therapist. Mostly based on the principles of cognitive behavioral therapy, these interventions can be accessed on internet-enabled desktop computers as well as mobile devices. Self-management interventions can be offered in *guided* or *unguided* form. Guidance often comprises electronic messages that are aimed at increasing adherence to the intervention.

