Self-management interventions for BPD have been tested in open-label pilot studies. However, in these studies, the interventions have been applied in a *blended format*, i.e., the intervention was used in addition to face-to-face psychotherapy. These interventions include the “DBT Coach” that can be used as an adjunct to Dialectic Behavioral Therapy (DBT) (12, 24) and “priovi®,” a program that is based on the principles of Schema Therapy (13). Offered in the traditional face-to-face format, both DBT and Schema Therapy have been shown to be effective in the treatment of BPD (25). The pilot studies on the aforementioned self-management interventions have concluded that they are well accepted by patients and can contribute to the reduction of symptoms of BPD. There is also an ongoing randomized study comparing an internet-delivered Dialectical Behavioral Therapy Skills Training (iDBT-ST) to a waitlist control condition in suicidal individuals engaging in heavy episodic drinking (26).

Experts in the treatment of BPD agree that self-management interventions should be used mainly in the blended format described above. Reasons for this preference include the opportunity for corrective experiences with respect to dealing with conflict and intense emotions in face-to-face psychotherapy. Another reason against using self-management interventions as a stand-alone therapy for BPD are safety concerns in a patient population that frequently engages in self-harm, suicide attempts, or other risky behaviors (13). On the other hand, a considerable proportion of individuals with untreated mental illness state that they prefer not to depend on a professional for the management of their disorder (11). Also, the aforementioned studies did not indicate possible harm that came from the use of self-management interventions in the treatment of BPD. A meta-analysis of studies with patients suffering from depressive symptoms found that compared with control conditions, harmful effects were less likely during the use of self-management interventions (27).

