### Outcome measures

All outcome measures are used in their German version. The main outcome measure is the Borderline Personality Disorder Severity Index (BPDSI) (31, 32), a clinician-rated semi-structured interview that is based on the DSM-IV criteria for BPD. It assesses the frequency of BPD-manifestations during the past 3 months. It has excellent psychometric properties: Cronbach's α = 0.85 in patients with BPD and interrater reliability of 0.98. It also has excellent criterion-validity and change sensitivity. All raters will have a bachelor or master degree in psychology, have experience in psychological diagnostic assessments and will have participated in a rater training. Before they are permitted to rate trial participants, raters will have to demonstrate adequate interrater reliability on an audiotaped interview. For each rater, we will also assess the interrater reliability of their third interview.

Secondary study outcomes and safety parameters that will also be assessed during the diagnostic interview include the presence of a diagnosis of BPD on the structured clinical interview for DSM-IV (SCID) (33, 34) and the presence of adverse or serious adverse events. The assessment of adverse events follows recommendations established in pharmacological research (36). Using a semi-structured interview, participants are asked whether they have experienced any of the following events during the observation period (past 33 months for baseline and since last assessment for all other assessments): life-threatening events (e.g., self-injury, drug intoxication, accidents, etc.), medical occurrences that require hospitalization and suicide attempts.

The following secondary outcomes and safety parameters are then assessed using self-report: severity of BPD using the BPD-Checklist (37), depressive symptoms using the 9-item Patient Health Questionnaire (PHQ-9) (38), symptoms of anxiety using a 7-item anxiety scale (GAD-7) (39), quality of life (QoL) using the five-dimension three-level version of the questionnaire developed by the EuroQoL group (EQ-5D-3L) (40) and negative effects of the intervention using the Negative Effects Questionnaire (NEQ) (41). Participants are also asked about the parallel use of psychotherapy.

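### The only stated stopping trigger pools all serious adverse events, so if other events are common and similar in both arms it could miss a significant excess of suicide attempts or life-threatening self-injury under priovi

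*Protocol article*

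**What the plan says.** The Data management section provides for internal audits by the steering committee and says: "During these audits, frequencies of serious adverse events will be compared between groups". The consequence follows: "The trial will be terminated prematurely if serious adverse events occur significantly more frequently in the intervention group". It adds: "No independent Data Monitoring Committee has been established however". No other stopping trigger is stated, and no test, level, counting unit or number of audits is given.

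Outcome measures lists what the adverse-event interview covers: "life-threatening events (e.g., self-injury, drug intoxication, accidents, etc.), medical occurrences that require hospitalization and suicide attempts". The Abstract gives the same three kinds of event as examples of SAEs. The Introduction says why safety needs care in this trial: "safety concerns in a patient population that frequently engages in self-harm, suicide attempts, or other risky behaviors".

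**The concern.** A pooled comparison treats a medical admission and a suicide attempt alike. SAEs that occur equally in both arms contribute nothing to the difference between arms but enlarge its standard error. An excess confined to suicidal behavior can then be clear on its own and unremarkable in the pool.

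The Abstract makes safety an aim of the trial, and self-harm and suicide attempts lead the risks that the Introduction names. The crisis plan and the clinician's written confirmation protect individual participants. The between-group comparison at audits is the only stated step that would act if the program itself raised risk.

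**Working it through.** **Inputs.** From the article: 100 participants per arm (Sample size), 1:1 allocation (Randomization), and 108 recruited by July 2018 (Abstract), taken here as 54 per arm. The stopping rule carries no figure of its own to reproduce. Assumed, because the article does not give them: all event rates and counts, participants with at least one event as the counting unit, and a 0.05 level. In the examples, suicidal events are suicide attempts or life-threatening self-injury, and other SAEs are counted only in participants without a suicidal event.

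**Formula.** With x₀ (control) and x₁ (priovi) participants with an event out of n per arm, and p = (x₀ + x₁)/2n, z = [(x₁ − x₀)/n] / √[2p(1 − p)/n]. The two-sided p-value from z is that of the uncorrected chi-square test. Fisher's exact test is given alongside.

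**Example at 54 per arm.** Nine participants in each arm have only another SAE; suicidal events are 1 (control) versus 8 (priovi).
- Suicidal events: p = 9/108 = 0.083; z = (7/54)/√(2 × 0.083 × 0.917/54) = 0.130/0.053 = 2.44.
- Class, 10 versus 17: p = 27/108 = 0.25; z = (7/54)/√(2 × 0.25 × 0.75/54) = 0.130/0.083 = 1.56.

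The difference is seven participants both times; only the standard error has grown.

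**Example at 100 per arm.** Fifteen other-SAE participants in each arm; suicidal events 5 versus 15, so the class is 20 versus 30.

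| Comparison | Chi-square, two-sided | Fisher, two-sided | z, one-sided | Fisher, one-sided |
|---|---|---|---|---|
| 54 per arm, class 10 vs 17 | 0.12 | 0.18 | 0.060 | 0.091 |
| 54 per arm, suicidal 1 vs 8 | 0.015 | 0.031 | 0.007 | 0.016 |
| 100 per arm, class 20 vs 30 | 0.10 | 0.14 | 0.051 | 0.071 |
| 100 per arm, suicidal 5 vs 15 | 0.018 | 0.032 | 0.009 | 0.016 |

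In both examples the class misses 0.05 on all four tests and the suicidal events meet it on all four.

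**Chance of triggering.** Exact binomial calculation at 100 per arm, z-test at two-sided 0.05, harm direction only. Class ranges run over the other-SAE rates shown and over whether other SAEs strike independently of suicidal events or never in the same participant.

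| Suicidal events, control vs priovi | Other SAEs, control vs priovi | Class | Suicidal events alone |
|---|---|---|---|
| 5% vs 15% | 10% to 30%, equal | 17–43% | 68% |
| 5% vs 15% | 2%, equal | 59–60% | 68% |
| 5% vs 15% | 10% vs 15% | 64–73% | 68% |
| 5% vs 15% | 20% vs 25% | 48–63% | 68% |
| 5% vs 10% | 10% to 30%, equal | 7–15% | 27% |
| 5% vs 10% | 10% vs 15% | 37–43% | 27% |

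By Fisher's test the first row is 14–36% against 59%. In the first row, with independent other SAEs at 10%, 20% and 30%, the class rule stays silent in 50%, 68% and 77% of the trials in which the suicidal excess is significant.

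**Either trigger.** Keeping the class rule and adding the suicidal comparison gives 70% to 73% in the first row. In the third row, with independent other SAEs, the chance rises from 64% (class alone) to 79%.

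**The case against.** The strongest objection is that the loss depends on other SAEs being about equal between arms. A program that raised suicidality could also raise crisis admissions and intoxications, and pooling then keeps or gains power, as the third and last rows of the second table show. This stands. A reader might infer that the class rule is least sensitive to the very harm the article names; the documents do not support that. They give no rates, and life-threatening intoxications and accidents may themselves result from the risky behaviors named in the Introduction.

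A reader might also take "About 75% of these costs are due to inpatient treatment" as evidence that diluting hospitalizations are frequent. It is a share of cost, not an event rate, and it concerns treatment for the disorder, so such admissions may overlap with suicidal crises. Overlapping events do not dilute.

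The 100-per-arm example lies close to the threshold. With 14 other-SAE participants per arm instead of 15, the one-sided z-test gives 0.049. With 5 per arm, the class is 10 versus 20 and the two-sided chi-square p is 0.048.

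Finally, the rule is a sufficient condition. It would be wrong to infer that the committee may not stop for another reason or may not look at events by type. But no such trigger is stated, and no independent committee is in place to supply one. Nor is this only detail left to a fuller document: the article itself fixes a trigger and its consequence.

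**Conclusion.** The point holds conditionally. The one stated trigger pools all SAEs. If other SAEs are common (10% to 30% in the calculations) and similar in both arms, it could stay untriggered through a significant excess of suicide attempts or life-threatening self-injury under priovi. For 5% versus 15% suicidal events at 100 per arm, the chance of triggering falls from 68% to between 17% and 43%. If other SAEs are rare, overlap with suicidal events or rise in parallel, the loss is small or absent, and pooling may even help. The documents cannot say which case applies. An added trigger can only raise the chance of a response, whichever case is true, so this is a cheap improvement to a stated rule rather than a demonstrated failure of it.

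**What to change.** Keep the class rule and add to Data management: at each audit, participants with a suicide attempt or life-threatening self-harm, including intentional intoxication, are also compared between groups by Fisher's exact test at the same level as the class rule; an excess in the priovi arm pauses recruitment and is reported to the ethics committee before the trial continues. At two-sided 0.05 and 100 per arm, this would pause at 6 versus 0, 8 versus 1, 10 versus 2 or 15 versus 5.

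The cost is a protocol amendment, for which the Ethics statement already provides, in a trial that is recruiting. The interview already asks about these kinds of event; the article does not say whether intent is recorded for an intoxication, so that may need a line on the form.

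False pauses become somewhat more frequent. With no true difference and 20% other SAEs, one look by Fisher's test at two-sided 0.05 triggers in about 1.7% of trials on the class alone and in 2.6% to 3.0% on either comparison. Over four equally spaced looks, with other SAEs at 10% to 30%, the figures are 3.4% to 4.7% against 4.5% to 7.5% by Fisher, and 6.4% to 7.2% against 10.2% to 12.3% by z-test. That is why the added trigger should pause recruitment rather than end the trial.
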